
##### Implementation outcomes

Primary outcomes for evaluating the school-to-school mentoring strategy (aim 2) are acceptability, appropriateness, and feasibility of the HSRC initiative, which we will measure using surveys and interviews. Other outcomes we will measure include the number of students reached and dose delivered. We will also ask implementers to complete a brief survey reporting their sociodemographic characteristics (e.g., biological sex, age, race, ethnicity, school affiliation, and years worked in education).

Acceptability, appropriateness, and feasibility of the HSRC initiative will be assessed among members of each school’s implementation team using three validated instruments: the Acceptability of Intervention Measure (AIM), the Intervention Appropriateness Measure (IAM), and the Feasibility of Intervention Measure (FIM) [58]. Each scale asks respondents to rate their level of agreement with statements about HSRC using a five-point Likert scale ranging from “completely disagree” to “completely agree.” For each measure, we will average item responses to produce a single score between 1 and 5, with higher values indicating more favorable perceptions of HSRC. Surveys will be administered before, during, and after HSRC, allowing us to examine changes in perceptions over time and compare differences between study conditions.

Within 4–6 weeks of the end of HSRC’s implementation, we will conduct interviews at each study school with the Extension agent (n = 20) and at least one other implementer (n = 20). We will use a semi-structured interview guide to ask implementers about the school-to-school mentoring strategy and the overall acceptability, appropriateness, and feasibility of HSRC. The interview guide will also address the five Consolidated Framework for Implementation Research (CFIR) domains – individual characteristics, innovation characteristics (e.g., the HSRC initiative), inner setting (e.g., school characteristics), outer setting (e.g., the community), and implementation process – to determine how the school-to-school mentoring strategy affected each of these domains [59, 60]. Interviews will be conducted in person or online, last 60–90 min, and be recorded.

To assess other implementation outcomes (number of students reached, dose delivered), implementers will be asked to track a variety of programmatic components, including which programs were delivered, the number of sessions delivered per program, the class size of each classroom receiving the selected programs, session attendance, and session duration. To evaluate the total number of students reached through HSRC programming, students will write their teacher's name on the student survey. We will determine dose delivered for participants in the study by using program metrics (number of sessions x session length) and summing them across the number of programs the students’ teachers received at the end of the school year.

### Analyses

#### Statistical analysis

For aim 1 (effectiveness), we will use univariate and bivariate statistics to determine the distribution of outcome measures and to identify relevant covariates [61]. To test intervention effects, students randomized to HSRC vs. the waitlist control group (independent variable) will be evaluated using a generalized linear model framework. Baseline scores will be added as a covariate, post-intervention scores as the outcome, and school as a clustering variable [62]. Other covariates (e.g., school size), identified in the preliminary bivariate analyses, will also be included in the model. If missing data occurs, we will mitigate potential biases by analyzing multiple imputed datasets under an intention-to-treat approach [63]. Analyses will be compared to per-protocol analyses [64].

For aim 2 (implementation), we will use a concurrent complementary mixed-methods approach to evaluate the impact of the school-to-school mentoring strategy on each implementation outcome [65]. Quantitatively, we will follow the same analysis approach described for aim 1. However, receiving the school-to-school mentoring strategy (yes vs. no) will be the independent variable, and implementation outcomes (e.g., acceptability, appropriateness, feasibility) will replace student outcomes.

Qualitatively, we will transcribe audio files from the interviews. Applying a directed content analysis and iterative categorization approach [66, 67], we will generate an a priori codebook that is based on our interview guide and the CFIR framework (two coders) [59, 60]. Queries will be performed for quotes assigned to each deductive code, then we will examine the relationship between the implementation strategy, barriers/facilitators, and implementation outcomes. As we are reviewing excerpts from the queries, we will note important findings and key points in ¼ −1-page written summaries. Finalized themes will be produced.

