### Procedure

#### Randomization

Schools will be randomized to receive one of four conditions: (1) immediate intervention and standard implementation (HSRC + SI), (2) immediate intervention and school-to-school mentoring (HSRC + M), (3) waitlist control and standard implementation one year later (WC + HSRC + SI), or (4) waitlist control and school-to-school mentoring one year later (WC + HSRC + M). To ensure balance across years, schools will be blocked into two cohorts of ten schools, with five receiving immediate intervention and five receiving waitlist control in each of the first two years. Additionally, three schools will receive standard implementation in year one, five in year two, and two in year three, whereas two schools will receive school-to-school mentoring in year one, five in year two, and three in year three (Fig. 1). The order of the ten conditions available each year will be randomized, and schools will receive them based on the order in which they enroll in the study (i.e., signed memorandum of understanding).

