A recent review identified three previous trials that used a DRCT design, none of which have published results, and none conducted in community-based settings [37–39]. Consequently, our study presents the first use of the DRCT within schools and within an Extension network. The DRCT was chosen not only for its scientific rigor, but also to help with some of the common challenges that occur when conducting research in communities. For example, control groups in effectiveness trials often receive no intervention or subpar implementation of the intervention (e.g., less attention) after serving as a control (i.e., waitlist control). In our study the waitlist control group will be randomized to the enhanced implementation strategy or standard implementation helping to ensure that schools in the waitlist control condition receive the same level of implementation support as schools that were randomized to receive the intervention immediately. Similarly, a delay in time to receiving an intervention (i.e., waiting one year) has the potential to affect implementation of that intervention. The DRCT balances both implementation strategy groups (enhanced vs standard) on whether they receive the intervention immediately or must wait one year, balancing this potential confounder across condition reduces this potential bias better than other types of designs often used in the community setting (e.g., step-wedge design). Consequently, findings from our trial will help to identify potential benefits and barriers to using the DRCT design in community settings, which can inform future research efforts.

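### Cohort (Aim 1) and delivery year and wait status (Aim 2) shape the randomization, but data-driven covariate screening decides whether they enter the models

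*Protocol article*

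**What the plan says.** The Randomization section restricts the allocation in two ways. For Aim 1, "schools will be blocked into two cohorts of ten schools, with five receiving immediate intervention and five receiving waitlist control"; this 5:5 split applies to both cohorts. For Aim 2 the number of schools per delivery year is fixed: "three schools will receive standard implementation in year one, five in year two, and two in year three", while "two schools will receive school-to-school mentoring in year one, five in year two, and three in year three".

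The Statistical analysis section compares HSRC with waitlist control in a generalized linear model. It then names the other fixed elements: "Baseline scores will be added as a covariate, post-intervention scores as the outcome, and school as a clustering variable". Anything further follows a selection rule: "Other covariates (e.g., school size), identified in the preliminary bivariate analyses, will also be included in the model". For the implementation aim, "Quantitatively, we will follow the same analysis approach described for aim 1", with mentoring yes/no as the independent variable. Cohort, delivery year and wait status are not mentioned in that section.

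The Discussion adds, on Aim 2: "The DRCT balances both implementation strategy groups (enhanced vs standard) on whether they receive the intervention immediately or must wait one year".

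**The concern.** An analysis should normally carry the factors by which the allocation was restricted. Here they enter only if a preliminary look at the data happens to flag them.

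In Aim 1 the two cohorts are measured in different school years. If they differ after baseline adjustment and cohort is not in the model, that difference sits in the between-school error. The blocking has already removed it from the treatment comparison, so the standard error is too large: power falls and the test becomes conservative.

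In Aim 2 delivery year is not equally distributed between the strategies. Any drift over the three years, such as growing familiarity with the program or the refinement of protocols that the Power analysis section expects during the study, passes in part into the mentoring contrast.

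**Working it through.** **1. The plan's own figures.** The 447 students for Aim 1 cannot be reproduced, because effect size, variance and clustering are only cited. As a guide, 447/20 = 22.35 students per school. With an assumed ICC of 0.03 the design effect is 1 + 21.35 × 0.03 = 1.64, and the detectable difference is 2.80 × √(4 × 1.64/447) = 0.34 SD. For Aim 2, d = 2.80 × √(2 × DE/(10m)). With m = 10 and ICC 0.03, DE = 1.27 and d = 0.446. Over teams of 8–10 and ICC 0.015–0.030 the range is 0.42–0.49, which contains the stated 0.45.

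**2. Aim 1: effect of leaving cohort out.** Assumptions: 20 schools of 22 students, ICC 0.03, residual variance 1, two-sided 5% test on school-level degrees of freedom. Let c be the cohort difference, in SD, that remains after baseline adjustment.

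- Variance of a school mean: v = 0.03 + 0.97/22 = 0.0741.
- Standard error of the arm difference: √(2 × 0.0741/10) = 0.122. On 18 df, 80% power needs an effect of 2.96 standard errors, or 0.36 SD.
- Each school lies c/2 from its arm's centre because of cohort. The residual sum of squares gains 20 × (c/2)² = 5c², so the estimated variance becomes v + 5c²/18. The true variance of the arm difference does not change, because cohorts are 5:5.
- Standard error inflation: √(1 + 5c²/(18v)).

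Simulation with 200,000 trials per setting:

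| c (SD) | SE inflation | Power, cohort out | Power, cohort in | Type I error, cohort out |
|---|---|---|---|---|
| 0 | 1.00 | 80% | 80% | 5.0% |
| 0.10 | 1.02 | 79% | 80% | 4.6% |
| 0.25 | 1.11 | 73% | 80% | 3.0% |
| 0.40 | 1.26 | 62% | 80% | 1.5% |

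At c = 0.10, 0.25 and 0.40, power with cohort out is 79%, 71% and 56% at ICC 0.01, and 79%, 75% and 66% at ICC 0.05. Including cohort when there is no shift costs about 0.3 points.

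**3. Aim 2: delivery year.** Mean year for standard implementation is (3×1 + 5×2 + 2×3)/10 = 1.9. For mentoring it is (2×1 + 5×2 + 3×3)/10 = 2.1. With year left out, bias = 0.2 × the yearly trend that remains after baseline adjustment.

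- A trend of 0.2 points per year gives 0.04 points, or 0.04/0.25 = 16% of the smaller target difference of 0.25 points.
- In SD units, trends of 0.1, 0.2, 0.45 and 0.9 per year give biases of 0.02, 0.04, 0.09 and 0.18.
- A bias of half of d = 0.45 would need 0.225/0.2 = 1.1 SD per year.
- Two-sided type I error without adjustment falls, to about 0.04 at 0.2 SD per year and 0.02 at 0.45, because the omitted trend also enlarges the residual variance.

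**4. Aim 2: wait status and cohort.** Let a be the number of cohort-1 waitlist schools that get standard implementation. The year totals then fix the standard:mentoring splits:

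| | Formula | a = 3 | a = 2 |
|---|---|---|---|
| Immediate | (8−a):(2+a) | 5:5 | 6:4 |
| Waitlist | (2+a):(8−a) | 5:5 | 4:6 |
| Cohort 1 | (3+a):(7−a) | 6:4 | 5:5 |
| Cohort 2 | (7−a):(3+a) | 4:6 | 5:5 |

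Exact balance on wait status is possible (a = 3), but strategy cannot then also be balanced on cohort.

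**5. Cost of block terms in Aim 2.** The four cohort-by-wait blocks of five schools are year 1 immediate, year 2 waitlist, year 2 immediate and year 3 waitlist. Fitting them is the same as fitting three-level year plus wait status. With a = 3 or 2 every block is 3:2 or 2:3, so the information is 4 × (3×2/5) = 4.8 against 10×10/20 = 5 without blocks. The variance ratio is 1.04. Residual df go from 18 to 15, and the t critical value from 2.10 to 2.13.

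**The case against.** The strongest reply is that nothing has been left out. The covariate list is open, names none of these factors as excluded, and could admit all of them. The article is condensed, and a full protocol or SAP may list the blocking factors. This stands as far as it goes: a reader might infer that the plan omits the design factors, and the text does not say so. What it does state is a rule, and under that rule a design factor enters only if the data flag it. In a school-mean simulation (ICC 0.03, shift 0.25 SD), a 5% screen on baseline-adjusted means picked cohort in only 33% of trials. Such a screen still recovered most of the power (about 78%), but the plan does not specify that screen.

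A second reply is that the sizes rest on assumptions. This also stands. No cohort shift, Aim 1 ICC or yearly trend is given. BMI z-score is scored against fixed norms and adjusted for baseline, so shifts of 0.25–0.40 SD between consecutive school years may not occur. At 0.1 SD the loss is only 1–1.5 points.

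Third, a reader might infer that mentoring is confounded with calendar year. That is too strong. Year two is 5:5, and years one and three have five schools each, so 3:2 is the closest split available. The imbalance is 0.2 years, type I error does not rise, and baseline scores from the same school year are in the model. The Power analysis section also calls Aim 2 a pilot.

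Fourth, a reader might infer that the Discussion's claim of balance on wait status is wrong. The year counts permit exact 5:5 balance, and balance on cohort is not claimed for Aim 2. Nor is the mid-year survey without a purpose: the Implementation outcomes section uses it to examine change over time.

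**Conclusion.** The point holds in a limited form. The stated covariate rule does not guarantee that the models contain the factors by which schools are allocated.

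For Aim 1 there is no bias. The possible loss is in precision and calibration, ranging from nothing with no residual cohort shift to 18 points of power at 0.40 SD (80% to 62%, ICC 0.03). It becomes material only from about 0.2 SD. The shift and the ICC are assumptions.

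For Aim 2 there is a built-in but small imbalance in delivery year, which passes 20% of any remaining yearly trend into the mentoring estimate. Wait status may well be balanced as the Discussion says; leaving it out would then affect precision only.

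Neither problem threatens the trial's validity. The change is worth making because it costs almost nothing and removes a data-driven choice from the primary models.

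**What to change.** In the Statistical analysis section, state that the following terms are included regardless of the bivariate analyses:

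- **Aim 1:** post-intervention score on baseline score, HSRC arm and cohort, with school as the cluster.
- **Aim 2:** implementation score on baseline score, mentoring arm and the four cohort-by-wait blocks (equivalently, three-level delivery year plus immediate/waitlist start), with school as the cluster.

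Screening can remain for other covariates. The change is to wording only and touches neither design nor data collection. It uses one school-level degree of freedom in Aim 1 and three in Aim 2. With the 3:2 blocks in the working, the Aim 2 standard error also rises by about 2% (√1.04). The year-two split by cohort should be confirmed from the allocation list first. With a = 1 or 4, two blocks would be 4:1 or 1:4, the information would fall to 2 × 1.2 + 2 × 0.8 = 4.0, and the variance ratio would be 5/4.0 = 1.25.

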### Study design

This study uses a hybrid type 2 implementation-effectiveness, cluster dual randomized controlled trial (DRCT; Fig. 1). DRCTs include two randomized controlled trials within the same study: one testing the intervention (i.e., HSRC) and one testing an implementation strategy [37–39]. DRCTs allow for rigorous testing of both the effectiveness of an intervention and the impact of an implementation strategy on outcomes, accelerating the translation of interventions into practice [37–39]. For the effectiveness aim (Aim 1), we will compare outcomes in ten Texas schools that receive HSRC with ten waitlist control schools (Fig. 1 in gray). For the implementation aim (Aim 2), ten schools will be randomized to receive a school-to-school mentoring program, and ten will receive standard implementation of the program (Fig. 1 in blue).

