#### Power analysis

For aim 1 (effectiveness), our final sample will include 25 students per school (*n* = 20 schools; 500 students total). With 50% of students in the intervention group and 50% in the control group, using effects sizes, variance, and cluster effects based on prior research [27], calculations indicate 447 students are needed to achieve a power of 0.80 to detect group differences in BMI z-score. We will recruit 500 students to account for a 5% loss to follow up.

Given that we have made additional modifications to the school-to-school mentoring strategy, we consider aim 2 (implementation) to be a pilot cluster randomized controlled trial. Best practices suggest that pilot studies focus on logistics and refinement of implementation protocols, which we will iteratively address through this study [68]. Still, based on our expected recruitment of 20 schools with 8–10-person implementation teams, using a beta of 0.8, a type I error rate of 0.05, and an intraclass correlation coefficient of 0.015–0.030, we are powered to detect a small-to moderate mean difference of 0.25—0.27 points on a 5-point scale (effect size of d = 0.45).

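### With 20 schools, both aims need small-sample inference and a fixed covariate list, and the Aim 2 detectable effect of d = 0.45 does not hold across its own stated inputs

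*Protocol article*

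**What the plan says.** The Study design section sets the number of clusters for Aim 1: "we will compare outcomes in ten Texas schools that receive HSRC with ten waitlist control schools". Aim 2 also splits the 20 schools ten and ten.

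The Statistical analysis section says that the HSRC comparison "will be evaluated using a generalized linear model framework", and then: "Baseline scores will be added as a covariate, post-intervention scores as the outcome, and school as a clustering variable". It adds: "Other covariates (e.g., school size), identified in the preliminary bivariate analyses, will also be included in the model". The number of such covariates is not limited, and the one example given is measured at school level. For Aim 2 it says: "Quantitatively, we will follow the same analysis approach described for aim 1". No estimator, reference distribution, degrees of freedom or variance correction is named for either aim.

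The Power analysis section plans Aim 1 on 447 students needed and 500 recruited: "our final sample will include 25 students per school". For Aim 2 it assumes 20 schools, teams of 8 to 10, type I error 0.05, ICC 0.015 to 0.030 and 80% power (written as a beta of 0.8). From these it claims to detect a difference of 0.25 to 0.27 "points on a 5-point scale (effect size of d = 0.45". The same section calls Aim 2 a pilot trial.

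**The concern.** Treatment varies only between schools, so its standard error rests on 20 school-level units. That leaves 18 degrees of freedom before any school-level covariate and one fewer for each one added. Methods justified for many clusters then tend to give standard errors that are too small and to compare them with a quantile that is too small. The wording used, a generalized linear model with a clustering variable, also describes software procedures whose default is an uncorrected sandwich variance with normal quantiles.

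The covariate rule makes this worse, because it can add several school-level terms and leaves their number unknown until the data have been examined. At stake is the false-positive rate of the primary BMI z-score test, and to a lesser extent of the Aim 2 comparisons.

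The Aim 2 power statement gives one effect size for a range of team sizes and ICCs. A reader will take it to hold over that whole range.

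**Working it through.** **1. Reproducing the Aim 2 figure.** All inputs come from the Power analysis section: 10 schools per arm, m = 8 to 10 per team, ICC 0.015 to 0.030, 80% power, type I error 0.05. A two-sided test is assumed, because sidedness is not stated.

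Design effect = 1 + (m − 1) × ICC. Standard error in SD units = √(2 × design effect / (10m)). Detectable d = (sum of the two quantiles) × standard error. The sum is 1.960 + 0.842 = 2.802 for the normal and 2.101 + 0.862 = 2.963 for t on 18 df.

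For m = 10 and ICC 0.030, the design effect is 1 + 9 × 0.030 = 1.27 and the standard error is √(2.54/100) = 0.1594. Then d = 2.802 × 0.1594 = 0.446, which reproduces the stated 0.45.

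**2. The rest of the stated range.** Power in the t column uses the noncentral t on 18 df.

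| m | ICC | Detectable d, normal | Detectable d, t18 | Power at 0.45, normal | Power at 0.45, t18 |
|---|---|---|---|---|---|
| 8 | 0.015 | 0.466 | 0.492 | 0.773 | 0.726 |
| 8 | 0.030 | 0.487 | 0.515 | 0.735 | 0.687 |
| 9 | 0.015 | 0.442 | 0.467 | 0.814 | 0.770 |
| 9 | 0.030 | 0.465 | 0.492 | 0.774 | 0.727 |
| 10 | 0.015 | 0.422 | 0.446 | 0.848 | 0.806 |
| 10 | 0.030 | 0.446 | 0.472 | 0.806 | 0.761 |

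With normal quantiles, 80% power at d = 0.45 is reached in three of the six settings. With t on 18 df it is reached in one. Neither method reaches it at 8 per team.

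**3. Type I error with 20 schools.** All runs are null trials at a nominal 5%. The article gives no student ICC and no covariate count, so both are assumptions here. School-level covariates were pure noise, cluster sizes were equal and outcomes normal.

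- *Exact reference.* A t statistic on 18 df compared with 1.96 rejects 6.6% of the time; on 16 df, 6.8%.
- *Exchangeable GEE, uncorrected sandwich, normal quantiles.* With 22 students per school (447/20 is about 22), ICC 0.02, baseline–outcome correlation 0.9 and 4,000 runs per setting: 8.3% with no school-level covariate, 8.8% with one, 10.9% with two, 12.0% with three. At ICC 0.05: 8.1% with none and 10.6% with two. With 9 per team and ICC 0.03 (Aim 2): 8.4% and 10.7%.
- *Ordinary least squares with a sandwich variance, normal quantiles.* With 25 students per school, ICC 0.03 and 6,000 runs per setting: 7.7%, 9.1% and 12.8% with zero, one and three covariates. A separate repeat with 20 schools of 25 gave 8.4%, 9.3% and 12.5%.
- *Covariates screened at p < 0.2 from five candidates*, GEE sandwich, normal quantiles, ICC 0.05: 10.4%.
- *Random school intercept, normal quantiles*, 40,000 runs per setting: 5.6% to 9.6% by ML and 4.9% to 6.8% by REML. The REML rate is 4.9% to 5.0% at 9 per team and ICC 0.015, so there is no inflation in that setting.

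**4. What repairs it.** Degrees of freedom are 20 − 2 − number of school-level covariates. A t reference alone does not repair the uncorrected GEE sandwich (6.4% to 9.7%). A school-means t test gives 4.8% to 5.1%, REML with t gives 3.4% to 4.9%, and a Mancl–DeRouen-corrected GEE with t gives 2.9% to 4.6%.

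**The case against.** The strongest reply is that the article does not make the choice being criticised. It names no estimator and no reference distribution, and its wording is compatible with a mixed model using corrected degrees of freedom. A condensed article commonly leaves such detail to the full protocol or analysis plan, neither of which is shown. This stands: silence on degrees of freedom is not an error, and the type I error point can only be conditional.

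A reader might infer from the match in step 1 that normal quantiles are in use. The figures do not show this. At 10 per team, t on 18 df also gives 0.446, at ICC 0.015. The SD is not stated; 0.25/0.45 and 0.27/0.45 imply 0.56 to 0.60. At 10 per team, the normal formula with SD 0.60 gives 0.253 to 0.268 points, and t with SD 0.57 gives 0.254 to 0.269. Both round to the stated range. Nor does a quantile used for planning fix the one used in analysis.

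It can also be said that d = 0.45 was meant for 10 per team, since the abstract's 200 implementers over 20 schools is 10 each. But the power statement itself gives 8 to 10.

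Finally, baseline adjustment could recover the shortfall. At a baseline correlation of 0.5, the largest value falls to 0.515 × √(1 − 0.25) = 0.446. That is a fair point, but no such correlation is among the stated inputs.

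On the covariate rule, screening followed by the bias-corrected GEE with t rejected 4.35%. Screening is therefore not shown to break the test once inference is corrected. What remains is that the rule is stated, uncapped and data-driven, and leaves the school-level degrees of freedom open.

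**Conclusion.** The point holds in two parts of different strength.

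For the analysis, it is a conditional warning plus one stated weakness. If uncorrected large-sample inference is used, type I error can exceed 5%: about 8% for a GEE or sandwich estimator with no school-level covariate, about 9% to 12% with one to three, and about 5% to 7% for REML with normal quantiles. A reader might go further and conclude that the planned tests run above 5%, or that every Aim 2 interval will be too narrow. The text supports neither, because the estimator is not named and one REML setting shows no inflation. The stated weakness is the open-ended covariate rule with only 20 schools. The sizes rest on assumed student ICCs and covariate counts. Because Aim 2 is a pilot, the primary BMI z-score test carries most of the weight. Label: cheap improvement.

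For the Aim 2 power figure, the statement is wrong as written. Its inputs give a detectable d of 0.42 to 0.49 with normal quantiles or 0.45 to 0.52 with t on 18 df. At 8 per team and ICC 0.030, power at d = 0.45 is 0.735 or 0.687. This assumes a two-sided test, equal team sizes and no gain from baseline adjustment.

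**What to change.** - Replace the bivariate screening with a short covariate set named in advance, with very few school-level terms.
- Name the small-sample inference for both aims. One option is a linear mixed model with a random school intercept, fitted by REML, with Kenward–Roger or Satterthwaite degrees of freedom. The other is GEE with a bias-corrected sandwich and t on schools minus school-level parameters. The simulations used t on 20 − 2 − covariates, not Kenward–Roger or Satterthwaite themselves. The corrected GEE became conservative as covariates were added (2.9% with three), which is a further reason to keep the list short.
- Restate the Aim 2 detectable difference with a t quantile across 8 to 10 per team and the full ICC range, and give the SD. If a gain from baseline adjustment is counted on, state the assumed correlation.
- Say which quantile lies behind the 447 students for Aim 1. If it was the normal one, which is not stated, the 80% power becomes about 75.5% with t on 18 df.

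This costs analysis wording and a software option, with no new data. The downside is slightly wider intervals and a slightly larger stated detectable difference.

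### Covariates for the effect model are picked by bivariate screening of the trial's own data; with 20 schools, screening on the post-test outcome can pull the HSRC estimate toward zero and cost power, by an amount the article does not let one fix

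*Protocol article*

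**What the plan says.** The Statistical analysis section of the Protocol article describes a first step for aim 1: "we will use univariate and bivariate statistics to determine the distribution of outcome measures and to identify relevant covariates". It then gives the model for the intervention effect: "Baseline scores will be added as a covariate, post-intervention scores as the outcome, and school as a clustering variable". The results of the first step feed the second: "Other covariates (e.g., school size), identified in the preliminary bivariate analyses, will also be included in the model".

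So the baseline score is the only covariate fixed in advance. School size is an example, not a commitment. The section gives no candidate list, selection threshold or maximum number, and does not say whether the screen uses baseline or post-test values. For aim 2 it says "Quantitatively, we will follow the same analysis approach described for aim 1", so the rule carries over.

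The design has 20 schools. On cluster size the Power analysis section says "our final sample will include 25 students per school". Schools are allocated in two cohorts of ten, "with five receiving immediate intervention and five receiving waitlist control in each of the first two years" (Randomization).

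**The concern.** This is a stated rule, not a detail left to an analysis plan that is not shown. Which covariates enter the primary model is decided by looking at the trial's own data.

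Schools are randomised, and school-level candidates, the only kind the article names, have 20 values. Chance imbalance between ten and ten schools is common. If HSRC works, an imbalanced covariate is correlated with the pooled post-test outcome partly because of HSRC itself. A screen on that outcome cannot tell this from a genuine prognostic relation. Each school-level covariate admitted also uses one of 20 - 2 = 18 between-school degrees of freedom. At stake are some attenuation of the primary estimate, some loss of power, and a primary model that is unknown until the data have been examined and may differ by outcome.

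**Working it through.** **The plan's own figure.** The Power analysis section says "calculations indicate 447 students are needed to achieve a power of 0.80 to detect group differences in BMI z-score", "using effects sizes, variance, and cluster effects based on prior research". The effect size, SD and ICC for aim 1 are not printed, so 447 cannot be reproduced. The recruitment margin can be checked: 447/0.95 = 471, and 500 × 0.95 = 475, so 500 covers the 5% loss with 475 - 447 = 28 students to spare. Working back with cluster size 447/20 = 22.35, design effect 1 + 21.35 × ICC, and d = (1.96 + 0.84) × √(4 × design effect/447), the detectable d is 0.27, 0.32 or 0.38 for ICC 0, 0.02 or 0.05. The rest therefore rests on assumed values.

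**Direction.** Let τ be the HSRC effect, D the chance difference in mean covariate between arms, and b the fitted slope of outcome on covariate within arms.
- Adjusted estimate = unadjusted estimate - b × D.
- The pooled covariate-outcome association is the sum of a part from b and a part proportional to τ × D.
- With τ > 0, if b and D have the same sign, the two parts add. The covariate tends to be selected, and the correction -bD is negative.
- If the signs differ, the two parts tend to cancel. The covariate tends to be left out, although adjusting would have raised the estimate.
- The selection is therefore lopsided toward shrinkage. By symmetry the same holds for τ < 0. With τ = 0, or when the screen uses the baseline score, the τ × D part vanishes and so does the lopsidedness.

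**Degrees of freedom.** Take a t-test on 18 - k df, with the noncentrality set to give power 0.80 at k = 0 and multiplied by √(1 - k/18) for chance imbalance. Useless school-level covariates then give power 0.774 (k = 1), 0.746 (k = 2), 0.715 (k = 3) and 0.644 (k = 5).

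**Simulation.** Assumed: 20 schools (5:5 in two cohorts), 22-24 students per school, ICC 0.03 unless stated, effect set to 80% power without extra covariates, t reference on residual school df, 2,500-6,000 trials per setting. Candidates are school-level and useless unless stated.

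| Screen against | Candidates, threshold | Mean estimate / true effect | Power |
|---|---|---|---|
| Baseline-adjusted outcome | 8, p<0.05 / 0.10 / 0.20 | 0.94 / 0.91 / 0.88 | 0.75 / 0.72 / 0.67 |
| Baseline-adjusted outcome | 6, p<0.05 / 0.20 | 0.953 / 0.909 | 0.763 / 0.719 |
| Raw post score, student-level test, baseline-post correlation 0.80 | 6, p<0.05 | 0.962 | 0.755 |
| Same, correlation 0.95 | 6, p<0.05 | 0.985 | 0.761 |
| Raw post score, correlation 0.80-0.95 | 8, p<0.05 to 0.10 | 0.96-0.99 | 0.76-0.79 |
| Raw post score | 1-3 | 0.97-1.00 | 0.77-0.81 |
| Baseline score | 6, p<0.05 | 1.008 (no bias) | 0.796 |
| Imbalance between arms | 6, p<0.05 | 1.004 (no bias) | 0.762 |

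Over the wider set of raw post-score settings (3-8 candidates, correlation 0.80-0.95), attenuation was about 0-6% and power about 0.70-0.80. Screening the baseline-adjusted outcome with many useless candidates reached about 13% and 14 points.

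Type I error under pooled screening was 0.043-0.058. Screening within arms gave no bias but a type I error of 0.063-0.075.

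**With a fixed covariate instead.** One pre-specified school covariate explaining 30% of between-school variance gave a ratio of 0.99-1.01, power 0.81-0.83 and type I error 0.046-0.056. Outcome screening in the same settings gave 0.905-0.990 and 0.74-0.79.

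**The case against.** The strongest reply is that the text does not say the screen uses post-test outcomes. It names neither the second variable of the bivariate tests nor the time point, and screening on baseline values gives no bias. This stands as a limit: the bias is conditional on a reading. It does not remove the point, because the sentence that introduces the screen is about the outcome measures, and nothing confines it to baseline. The other readings are not all free either: imbalance screening costs about 2-4 points of power, and within-arm screening raises type I error.

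A second reply is that the larger losses need eight useless candidates screened against a baseline-adjusted outcome, whereas the article names one candidate and describes bivariate tests. This also stands. With few candidates, or a post score that tracks baseline closely, the effect is slight. Screening can also find useful covariates: with five candidates, two of them strongly prognostic, and ICC 0.05, power stayed at 0.80-0.82, though about 0.90 was available had those two been fixed in advance.

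A reader might infer three stronger things that the documents do not support.
- That the planned 80% power will not be reached: the aim 1 inputs are not given, so this cannot be shown.
- That false positives increase: pooled screening does not cause this when degrees of freedom are counted. An inflation argument would need a large-sample standard error that the article never names.
- That a confirmatory aim 2 analysis is compromised: the Power analysis section treats aim 2 as a pilot.

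**Conclusion.** The concern holds as a modest point about pre-specification. The article states a data-driven rule for the covariates of the primary model. If the screen is on the pooled post-intervention outcome, the direction of the harm is clear: attenuation toward zero and lost power.

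The size is a range that rests on an assumed number of candidates, threshold, ICC and baseline-post correlation. It is roughly 0-6% attenuation and 0-10 points of power when the raw post score is screened. It rises to about 13% and 14 points only when a baseline-adjusted outcome is screened with many useless candidates. Under a baseline screen there is no bias. The change is worth making because it is cheap and removes the dependence on which reading applies.

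**What to change.** Replace the screening rule with a short covariate list fixed before post-test data are seen:
- the baseline value of the outcome;
- cohort, as the blocking factor;
- at most one or two school-level variables already held, such as school size. The Study setting and school recruitment section says state education data are used to identify schools by size, rurality, socioeconomic status and racial/ethnic composition.

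Keep bivariate screening for description or a labelled sensitivity analysis, and make the same change for aim 2, since it inherits the approach.

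The cost is analysis wording only; no data collection changes. There are two downsides. A strong prognostic covariate not on the list is left to the sensitivity analysis. A fixed school-level covariate that proves useless also costs power (0.80 to 0.774 for one, 0.746 for two, on the calculation above), which is why the list should be short and chosen for expected prognostic value.
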